## Abstract

**Background:**

Knee osteoarthritis (OA) is a major cause of disability as well as a burden on healthcare resources. Tai chi has been proposed as an alternative and complementary treatment for the management of knee osteoarthritis, but there appears to be no consensus on its usefulness. This study aims to develop an innovative tai chi rehabilitation program (ITCRP) for patients with knee OA, and to investigate the effect of ITCRP intervention on a range of outcomes including pain, function, balance, neuromuscular response, and biomechanics in knee OA.

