### Participants

#### Inclusion criteria

Participant selection will be based on the Classification Criteria of the American Rheumatism Association for knee OA
[15].

1. Men or women, with diagnostic criteria of definite OA of the knee (unilateral or bilateral) according to radiography with reports of pain symptoms for at least 3 months;

2. Mild to moderate knee OA (Lequesne Knee Score = 1 to 7);

3. Age 60 to 90 years;

4. Medication not expected to change during the study period;

5. Availability: three times a week over a period of 12 months.

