#### Exclusion criteria

Participants with any of the following conditions will be excluded:

1. Inability to communicate in English, French or Chinese;

2. Presence of pain at rest or at night;

3. A medical condition involving hip or knee trauma, or intra-articular hip, or knee injection within one month;

4. Exercise-induced or uncontrolled angina within three months, or severe dyspnea at rest;

5. Terminal illness;

6. Uncontrolled hypertension;

7. Other illness, judged by the patient or study physician to make participation in this study inadvisable;

8. Bilateral total hip or knee arthroplasties;

9. Current rehabilitation treatment or previous corticosteroids injection within the last 12 months or any other pain-related treatment besides medication for arthritis;

10. A Mini-Mental State Exam score of 23 or lower
[16];

11. Surgery planned in the next year;

12. Obesity (body mass index >30 kg/m^2^).

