#### Secondary outcome measures

1. Berg balance scale
[25]. This is a widely used clinical test of a person’s static and dynamic balance abilities, which comprises a set of 14 simple balance related tasks, ranging from standing up from a sitting position, to standing on one foot. Total score ranges from 0 to 56, with 0 to 20 corresponding to a high fall risk, 21 to 40 a medium fall risk, and 41 to 56 a low fall risk.

2. Time up and gotest
[26]. This reflects the time that a person takes to rise from a chair, walk three meters, turn around, walk back to the chair, and sit down. Times up to 10 secondsindicate normal mobility, 11 to20 seconds are within normal limits for frail elderly and disabled patients, and times longerthan 20 seconds signify thatthe person needs assistance and indicates further examination and intervention.

3. Functional reach test
[27]. This is a dynamic rather than a static test and measures a person’s 'margin of stability’ as well as the ability to maintain balance during a functional task. The distance between the start and end points is measured using the head of the metacarpal of the third finger as the reference point. Three trials are done and the average of the last two is noted.

4. Muscle strength test of knee and ankle. The muscle strength on the dominantknee and ankle joint will be tested using an isokinetic dynamometer (850–000, Biodex, New York, USA). Knee muscle strength and endurance will be determined using the method used in our previous tai chi intervention studies
[18,28]. Participants will perform three maximum concentric contractions for knee extensors and flexors at the angular velocities of 30°/s. The highest peak torque indicating muscle strength will be normalized by kilogram of body weight. The dynamic endurance of the knee extensors and flexors will be assessed by measuring 40 repeated maximum isokinetic contractions with an angular velocity of 180°/s. The work from a knee angle of 80° to 10° will be recorded for each contraction. The endurance index is defined as the ratio of the work done during the last five contractions over the first five contractions. Ankle muscle strength will be measured as in our previous studies

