[18,28]. Ankle dorsiflexor and plantarflexor strength will be measured at an angular velocity of 30°/s. Participants will be instructed to push afoot away from themselves and then pull it toward themselves at the maximum velocity for each action. Peak torque will be determined as the highest torque generated from the three trials. In addition, the relative peak torque will be analyzed.

5. Proprioception test of knee and ankle. The measurement method has been reported in our previous studies
[29]. Knee and ankle proprioception will be tested using an electrically driven movable frame. During the tests, the participants will sit on a chair with their dominant legs supported by the frame. The leg can be passively moved in a flexed or extended direction at a velocity of 0.4°/s. Once the participant is able to detect the motion of the leg, he or she will press a handheld stop button and confirm the direction of the motion. The rotation angles of the frame will be determined as the threshold for the detection of the knee and ankle joint. The mean values of the three trials in one direction will be used for the analysis.

6. Neuromuscular response. Neuromuscular response indicated by muscle latency will be assessed through the use of electromyography (EMG) of the leg muscles, while an unexpected perturbation is applied to the ankle. We have used the method in our previous study
[18]. A customized trap door with an 18° tilt angle will be used to generate an ankle inversion perturbation while subjects stand barefoot on trap doors. The Bagnoli-8 EMG system (DS-B04, Bagnoli™-16 Desktop EMG system, Delsys Inc., Boston, MA) will be used to collect surface EMG signals in four muscles (rectus femoris, semitendinosus, gastrocnemius, and anterior tibialis) of the right leg and the onset signals at the trap door tilting. To reduce anticipatory effects, both feet will be randomly tilted at least seven times. The onset latency of the muscles refers to the time interval in milliseconds (ms) between trapdoor initiation and the first rising front of the EMG burst from the baseline. The EMG onset will be determined visually by an experienced researcher.

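### Strength, proprioception and EMG are tested on a leg chosen by dominance or by side, not by the affected knee, so an unknown share of participants with unilateral OA is measured on a knee without OA

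*Protocol article*

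**What the plan says.** Under Inclusion criteria, the protocol article admits "definite OA of the knee (unilateral or bilateral) according to radiography", so one-sided disease is enough to enter.

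Under Secondary outcome measures, three items fix the leg to be tested:

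- Item 4 (strength): "The muscle strength on the dominantknee and ankle joint will be tested using an isokinetic dynamometer".
- Item 5 (proprioception): "the participants will sit on a chair with their dominant legs supported by the frame".
- Item 6 (EMG onset latency): signals come from "rectus femoris, semitendinosus, gastrocnemius, and anterior tibialis) of the right leg". Both feet are tilted in random order, but the recording is specified for the right leg only.

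The article nowhere links the tested leg to the affected or more symptomatic knee, and it defines no index knee. The only exclusion that names joint replacement is item 8, "Bilateral total hip or knee arthroplasties".

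The Abstract sets the aim as the effect on "outcomes including pain, function, balance, neuromuscular response, and biomechanics in knee OA".

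**The concern.** The trial asks what the program does in knee OA, and these three items are meant to show its effect on strength, joint sense and muscle response. If the only OA knee is on the non-dominant side, the strength and proprioception values come from a knee without OA. If the only OA knee is the left one, so does the EMG latency.

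Two lesser consequences follow from the same rules:

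- Exclusion 8 bars replacement only when it is bilateral. Under that item a person with one replaced knee and OA in the other can enter, and the side rule could then select the replaced joint.
- The two side rules differ. In left-dominant participants, strength and proprioception come from one leg and EMG from the other.

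At stake is how the knee-specific secondary outcomes can be read. A small or null difference could mean that the program has little effect on OA knees, or that part of the sample was measured on a knee with less to gain. A later analysis cannot recover data from a knee that was never tested.

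**Working it through.** The article gives no effect size, standard deviation or power for these outcomes, so there is no figure to reproduce. The check has two parts.

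**1. Do the rules collide?** Eligibility allows one affected knee. The tested leg is the dominant one (items 4 and 5) or the right one (item 6). Neither rule depends on which knee is affected. With unilateral disease, the tested knee is therefore the OA knee only when the two sides happen to coincide.

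**2. How large could the effect be?**

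Inputs from the article: N = 140 and 1:1 allocation (70 per arm), from Study design; significance at 0.05, from Statistical analysis (two-sided is assumed, since sidedness is not stated).

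Assumptions, none given in the article:

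- u = share of participants with unilateral OA.
- q = chance that the OA knee is not on the tested side; q = 0.5 if side is unrelated to dominance (for EMG, if left and right are equally likely).
- r = response of a non-OA knee as a fraction of the response of an OA knee.
- The standard deviation is the same in both kinds of knee.

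Formulas with q = 0.5:

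- Share tested on a non-OA knee = u/2.
- Factor on the mean effect: f = 1 − (u/2)(1 − r). This is 1 − u/2 for r = 0, 1 − u/4 for r = 0.5, and 1 for r = 1.
- Equivalent sample size = 140 × f².

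| u | Tested on a non-OA knee, of 140 | r = 0: f, equivalent N | r = 0.5: f, equivalent N | r = 1: f, equivalent N |
|---|---|---|---|---|
| 30% | 21 | 0.85, 101 | 0.925, 120 | 1, 140 |
| 50% | 35 | 0.75, 79 | 0.875, 107 | 1, 140 |
| 70% | 49 | 0.65, 59 | 0.825, 95 | 1, 140 |

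For example, with u = 50% and r = 0: 140 × 0.75² = 78.75.

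If q is allowed to run from 0.4 to 0.6 and u from 20% to 60%, the number tested on a non-OA knee runs from about 11 (140 × 0.2 × 0.4) to about 50 (140 × 0.6 × 0.6).

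As an illustration in terms of power, take an assumed standardized effect of d = 0.5 in OA knees. Power = Φ(d × f × √(70/2) − 1.96). With f = 1 this is Φ(2.958 − 1.96) = 84.1%.

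| u | Share on a non-OA knee | Power, r = 0 | Power, r = 0.5 |
|---|---|---|---|
| 20% | 10% | 75.9% | 80.2% |
| 40% | 20% | 65.8% | 75.9% |
| 60% | 30% | 54.4% | 71.0% |

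The loss exists whenever the non-OA knee responds less than the OA knee. Its size depends on u and r, and the article gives neither.

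**The case against.** The strongest reply is that the size is unknown and may be small.

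- **Unilateral share.** If most participants have bilateral disease, few are affected. This stands. A reader might infer that many participants are measured on a healthy knee, but the article gives no laterality figures, and the most that can be said is about half of an unknown share.
- **Response of the other leg.** The program is whole-body stepping, and the Discussion credits tai chi with a neuromuscular training effect in general terms, not only in diseased knees. In people aged 60 to 90 the other leg may well gain too. This stands, and it is why the no-response column is the pessimistic end of a range that reaches no loss.
- **Validity.** A reader might infer bias, or that a null result would be uninterpretable. Neither follows. Both arms are measured by the same rule, and the comparison remains a valid randomized contrast of dominant-leg or right-leg function in people with knee OA. It answers a somewhat different question from function of the affected knee.
- **Reach.** The VAS, WOMAC and Lequesne scores do not depend on the tested leg. Items 4 and 5 also cover the ankle, and item 6 perturbs the ankle and records two lower-leg muscles among its four, so the argument is weaker there. This stands.
- **Stated emphasis.** A reader might take neuromuscular control of the OA knee to be the trial's declared novelty. The Background stresses neuromuscular control without tying it to the affected knee, and Strengths and limitations names the OA-specific program, the duration and the 3D biomechanics instead.
- **Replaced joints and mixed sides.** Nothing indicates how often a replaced joint would be tested. The dominant-versus-right mismatch matters only for left-dominant participants, and no stated analysis combines these measures within a person.
- **Comparability.** The methods follow the team's earlier studies, which is a plausible reason for a fixed leg, although the article does not state it.

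None of this removes the mismatch itself. The tested leg is a stated rule, not a detail left to a fuller document.

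**Conclusion.** The point holds as a moderate one. As written, the rules will measure some participants with unilateral OA on a knee without OA, and they could measure a replaced joint. The share is u/2 if side is unrelated to dominance, with u unknown.

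The consequence is dilution and harder interpretation of the knee-specific parts of secondary items 4 to 6. Over u = 30% to 70%, the retained effect is 65% to 85% if the non-OA knee does not respond, 82.5% to 92.5% if it responds by half, and 100% if it responds fully. These figures rest on the assumptions listed with the calculation, chiefly independence of side and dominance and equal spread in both kinds of knee.

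The documents support no claim of between-arm bias and none about the primary outcomes. The change is worth making because it is cheap and cannot be made after baseline testing.

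**What to change.** Define an index knee at screening, before baseline testing: the OA knee if disease is unilateral, the more symptomatic OA knee if it is bilateral, and never a replaced joint. Use that side for the strength, proprioception and EMG tests at baseline, 6 months and 12 months. Record laterality of OA and leg dominance for every participant, so that dominance can be used as a covariate.

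The cost is one line in each test description and a few case-report fields. Devices and the number of tests stay the same. The small downside is less direct comparability with the team's earlier studies, if those used the dominant or right leg.

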**Methods/Design:**

We will conduct a prospective, single-blind, randomized controlled trial of 140 individuals with symptomatic knee OA. Patients will be randomly assigned into either an ITCRP group or a control group. The ITCRP group will participate in tai chi two or three times a week for 6 months. The control group will receive health education. After the 6-month intervention period, there will be a 6-month follow-up period with no active intervention in either group. The primary and secondary outcomes will be assessed at baseline, 6 months, and 12 months. Primary outcome measures will be a visual analog scale for pain, the Western Ontario and McMaster Universities Osteoarthritis Index,and the Lequesne Knee Score. The secondary outcome measures will include the Berg balance scale, knee and ankle proprioception, neuromuscular response, and 3D functional biomechanics. Furthermore, adverse events will be recorded and analyzed. If any participants withdraw from the trial, intention-to-treat analysiswill be performed.

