### Withdrawal criteria and management

Study patients will be allowed or asked to withdraw from the study if:

1. The participant or his or herlegal representative makes such a request.

2. The participant develops a serious disease, such as heart disease or stroke and, in the investigator’s opinion, it is not suitable to continue.

3. The participant has an adverse reaction related to the tai chi exercise program.

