#### Control group

The participants in the control group will attend one 60-minute group session per week. The session will consist of a 30-minute lecture, followed by a 30-minute discussion. The lectures will cover health-related topics, such as OA, aging, nutrition. The participants in the control group will be asked to maintain their previous lifestyle and not take part in any other regular rehabilitation programs.

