### Outcome measures

All outcome measures will be administered by the main research assistant, blind to group allocation, at 2 weeks (baseline), 6 months (follow-up 1, at the end of intervention) and 12 months (follow-up 2). Demographic information will include age, sex, ethnicity, marital status, educational status, accommodation type and postcode. Clinical information will also be obtained from the patients’ clinical records by a member of their hospital research team.

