[33]. We will use the Barthel Index, which consists of tenitems to measure a person’s daily functioning, specifically the activities of daily living and mobility. The items include feeding, moving from wheelchair to bed and return, grooming, transferring to and from a toilet, bathing, walking on level surface, going up and down stairs, dressing, continence of bowels and bladder. Total scores are calculated by summing the individual item scores. Scores are weighted and range from 0 (dependence) to 100 (independence). Scores of 0 to 20 indicate total dependence; 21 to 60, severe dependence; 61 to 90, moderate dependence and 91 to 99, slight dependence.

10. Short Physical Performance Battery
[34]. This is a tool designed to quantify physical performance and decline over time. The test focuses primarily on lower extremity function and includes a 4-meter walk to measure gait speed, one chair stand (followed by five timed chair stands, if the first is successfully completed), and balance stands with the feet in different positions for 10 seconds each. Scores are weighted and range from 0 (worst performance) to 12 (best performance). Scores of 0 to 3 indicate severe limitations; 4 to 6, moderate limitations; 7 to 9, mild limitations and 10 to 12, minimal limitations.

11. SF-36 Health Survey
[35]. This is a multi-purpose, short-form health survey with only 36 questions. SF-36 items cover eight domains: physical functioning, role limitations due to physical health problems, bodily pain, general health, vitality, social functioning, role limitations due to emotional problems and mental health. Higher scores indicate higher levels of health.

12. Adverse events. A record will be made of any side effects and possible adverse reactions arising from the ITCRP.

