### Statistical analysis

Statistical analyses will be performed using SPSS 17.0 and Microsoft Excel 2007 software. Data will be expressed as mean ± standard deviation. Changes in variables before and after training and between groups will be analyzed. The main analysis will be to compare the efficacy of ITCRP group with the control group, including the primary and secondary outcomes, using 2-way analysis of variance (group × time). We will conduct an intention-to-treatanalysis if participants are lost to follow-up. The basic intention-to-treat principle is that participants in trials should be analyzed in the groups to which they were randomized, regardless of whether they received or adhered to the allocated intervention. Statistical significance was assumed at *P* less than 0.05.

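### The adverse-event outcome is defined by attribution to the tai chi programme, which no control participant's event can meet and which conflicts with other parts of the protocol article

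*Protocol article*

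**What the plan says.** Secondary outcome measures, item 12, is the only place where the article says what the adverse-event outcome consists of: "A record will be made of any side effects and possible adverse reactions arising from the ITCRP".

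Four other places bear on it:

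- **Abstract, Methods/Design:** "Furthermore, adverse events will be recorded and analyzed". No arm or cause is specified.
- **Outcome measures, opening paragraph:** "All outcome measures will be administered by the main research assistant, blind to group allocation". Adverse events are one of the outcomes listed below that sentence.
- **Statistical analysis:** "The main analysis will be to compare the efficacy of ITCRP group with the control group, including the primary and secondary outcomes".
- **Withdrawal criteria and management:** one criterion is specific to the programme ("The participant has an adverse reaction related to the tai chi exercise program"), and another could apply in either arm ("The participant develops a serious disease, such as heart disease or stroke").

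The Control group section describes the contact ("The participants in the control group will attend one 60-minute group session per week") and mentions no recording of adverse events.

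**The concern.** Item 12 sets two conditions. An event must be attributed to a cause, and that cause is present in only one arm. A definition of this kind suits a list of suspected reactions to a programme. It does not suit an outcome in a randomized comparison, because randomization protects a comparison only if events are ascertained in the same way in both groups.

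Participants are 60 to 90 years old with symptomatic knee osteoarthritis. Pain flares, falls and intercurrent illness can be expected in both arms whatever the treatment. Without a matching control record, a background event in the tai chi arm may be blamed on the programme, or a real harm may be set aside as unrelated. The data could not tell these apart.

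Timing matters too. Under Trial status the article reports that patients are being recruited. A statistical analysis plan can choose how to tabulate events, but it cannot recover control events that nobody was asked about.

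**Working it through.** The article gives no adverse-event rate, safety margin or safety power, so there is no figure to reproduce. The check sets the passages side by side.

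**1. Can a control event satisfy item 12?** The event must arise from the ITCRP. Controls receive weekly health education and not the ITCRP. The answer is no, whatever the event is. With 140 participants allocated 1:1, about 140 / 2 = 70 people fall outside the definition from the moment of randomization.

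**2. Does item 12 agree with the abstract?** No. The abstract's statement covers adverse events in general, while item 12 covers only those attributed to one arm's intervention. Under the abstract, about 70 and 70 participants can be compared. Under item 12, the record in one group of about 70 is set against a count that is zero by definition.

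**3. Does item 12 agree with blinded collection?** No. An assessor who does not know the allocation cannot decide whether an event came from the ITCRP without first learning whether the participant was in that arm. If the blinded assessor collects this outcome, either the filter or the blinding has to give way. If adverse events are thought not to be something one administers, and so fall outside that sentence, then the article names nobody who collects them.

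**4. Does item 12 agree with the planned comparison?** Not if the Statistical analysis section is taken at its word. It compares the groups on the secondary outcomes, and item 12 is listed as one. A risk difference or ratio computed from the item 12 record would have no valid comparator.

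**5. Does any other section define control-arm capture?** No. The Control group section says nothing about it. The withdrawal criterion for serious disease would bring some events in either arm to notice, but only those that lead to withdrawal.

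In sum, the one operational definition excludes controls, three other statements imply a wider collection, and no section says which governs.

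**The case against.** **The article never says control events will be ignored.** A reader might infer from item 12 that controls will not be asked and that the control arm will have no safety data. The documents do not support that. Item 12 states what will be recorded, not what will be left out. The abstract's unrestricted statement, the blinded collection of outcome measures and the arm-neutral serious-disease criterion all point towards wider capture. This objection stands, and it limits the finding to a conflict between passages.

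**Collection forms, schedules and safety tables belong in the full protocol or analysis plan.** This is correct, and their absence from a journal article is no defect. The full protocol may well settle the matter. But the article does not merely omit detail here. It states a definition, and that definition is restrictive and disagrees with the article's own abstract.

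**Adverse events will not go through analysis of variance.** The article plans the comparison "including the primary and secondary outcomes, using 2-way analysis of variance", and a reader might infer that event counts are to be analysed as means. The same sentence opens by speaking of efficacy, so that reading is strained, and the method for safety data is ordinary analysis-plan content. The point is at most secondary.

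**Symptom worsening is not wholly without a comparator.** This is also correct. Pain and function at 6 and 12 months are measured in both arms by the visual analog scale and WOMAC, and balance by the Berg scale and related tests. A reader might infer that the plan would hide a reduction in falls, but falls are not a listed outcome. What these scales miss is a discrete event between visits, such as an injury or an acute illness.

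**Unequal contact would not by itself explain an imbalance.** The weekly practice forms in the tai chi arm record times and durations of practice; nothing says that they capture events. Controls also have weekly contact during the intervention. It would be speculation to say that events surface only in the tai chi arm.

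**Conclusion.** The finding holds as an inconsistent and badly fixed outcome definition, of moderate severity. Item 12 cannot be met by any control event. It conflicts with the abstract and with blinded outcome collection, and with the between-group comparison if secondary outcomes are taken to include it. Control-arm capture is left undefined.

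Its size is structural. If item 12 governs, the control count is zero by definition for about 70 of 140 participants and no valid between-arm comparison of harms exists. If the abstract governs, the comparison is available and only the wording needs repair. The documents do not settle which applies. They give no event rate either, so any number put on a spurious excess or on missed events would rest on an invented rate, and none is offered here.

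The moderate rating reflects that the stated aims concern pain, function, balance and biomechanics, that no between-arm safety hypothesis is stated, and that a short rewording corrects the problem. It is still worth acting on during recruitment, because uncollected events cannot be restored at analysis. The conclusion assumes that the full protocol, which is not shown, does not already contain a broader rule. If it does, the article's wording should be brought into line with it.

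**What to change.** Reword item 12 and reconcile it with the abstract, the Outcome measures paragraph and the Statistical analysis section:

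- **Scope:** record every adverse event in both arms, whatever its suspected cause.
- **Ascertainment:** use the same question, form and schedule in both arms, for example at the weekly contacts that each arm already has during the intervention and at the 6- and 12-month assessments. The weekly activity forms and monthly gatherings after month 6 are described only under the ITCRP group. Events should not be gathered there unless controls have matching contact.
- **Relatedness:** hold it as a separate field, not as a condition for recording. Someone other than the blinded assessor should complete it, so that blinding is kept.
- **Reporting:** give the number and proportion of participants with at least one event by randomized arm, with a risk difference and 95% CI. State that the efficacy analysis of variance does not apply to this outcome.

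The cost is one short form added to contacts that already exist, plus the time to complete and enter it. Events among controls already enrolled may be only partly recoverable by asking back, so the date of the change should be recorded.
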